### EUS-FNA procedure

#### Operator

The procedures will be conducted by experienced operators who have performed at least 100 EUS-FNA procedures prior to the initiation of the study.

#### Observation

An EUS device with a convex transducer will be used to observe the target lesions through the lumen of the gastrointestinal tract. In Doppler mode, the EUS device will be used to check whether any large blood vessel crosses the planned puncture route.

#### Puncture

The maximum diameter of the lesion in the direction of the puncture route will be measured in order to determine the position of the puncture needle stopper. Puncture will be performed after retracting the stylet by approximately 5 mm.

#### Strokes

While applying negative pressure using a 10-mL syringe and observing the puncture needle under ultrasound guidance in real time, the needle will be moved back and forth within the lesion approximately 20 times.

#### Processing of specimens

The stylet will be re-inserted into the needle to eject the collected tissues from inside the needle. The specimens will be submitted in a container of formalin.

#### Procedure completion

It is not necessary to use the same needle for subsequent punctures. The operator may freely select the puncture needles for subsequent punctures depending on the size and number of specimens obtained during the first puncture. In this study, only the specimen obtained with the first puncture will be used to evaluate the pre-specified outcomes. The EUS-FNA procedure will be considered complete when the operator determines that sufficient specimens have been collected at the second or subsequent punctures.

### Histopathological diagnosis

Histopathological diagnosis will not be based on cytology but on histology. Specimens fixed with formalin will be embedded in paraffin blocks. Immunostaining and nuclear staining will be performed as needed. In this study, the specimens obtained at the first puncture will be sent to Hoken Kagaku West Japan Co., Ltd, who will prepare the specimens and send them to Kyoto Prefectural University of Medicine for diagnosis. Two experienced pathologists who have performed at least 1000 cytology and histology evaluations of EUS-FNA specimens will assess the specimens independently. The two pathologists will be blinded to the type of needle used. Histology evaluation will be performed to determine: (i) sample cellularity, (ii) preservation of tissue architecture, and (iii) histologic diagnosis. Sample cellularity is classified as rich (≥ 5000 cells), moderate (100–5000 cells), or poor (< 100 cells).

### Final diagnosis

For the purpose of this study, diagnosis is defined as malignant or benign mass. For patients receiving surgical resection, the final diagnosis will correspond to the pathological diagnosis established based on the resected sample. For patients with non-resection, the final diagnosis will be made based on the results of repeat EUS-FNA biopsy, diagnostic imaging such as computed tomography, magnetic resonance imaging, and positron-emission tomography, and observation of the clinical course for at least 1 year. Kamata et al. reported the final diagnosis of 61 patients (27%) was confirmed by surgical resection in 225 patients [10]. So, we expect 30% of patients will receive surgical resection.

### Follow-up period

For the purpose of the present study, all patients will be followed-up for at least 1 year after EUS-FNA.

### Sample size calculation

There have been no reports on the rate of correct diagnosis of pancreatic masses evaluated by EUS-FNA using the 22G Franseen needle. However, a previous study focusing on puncture needles designed to sample sufficient tissue for core biopsy reported that the rate of correct diagnosis was 75% for the conventional needle (EchoTip Ultra needle) compared to 80% for the specially designed EchoTip ProCore needle [10]. Assuming that the rate of correct diagnosis is higher when using the Franseen needle than when using the EchoTip ProCore needle, we expect the rate of correct diagnosis of pancreatic mass malignancy to be 85% when EUS-FNA is performed using the Franseen needle. A sample size of 500 participants (250 per group) would provide a power of 80% (1 − β) considering a two-sided significance level of α = 0.05 (chi-square test) for between-group comparisons of diagnostic rate. Assuming that approximately ten participants per group will have to be considered ineligible for inclusion in the final analysis, the target sample size in this study is established at 520 participants (260 per group).

### Data collection

Data will be collected using a standardized data entry form and entered into the data management system. Figure 2 provides an overview of the types of data collected and the timing of data collection.

**Fig. 2 Fig2:**
[figure not shown]
Standard protocol items (SPIRIT): schedule for data collection. ^1^Blood tests to be performed include blood counts, total bilirubin, albumin, alanine aminotransferase, aspartate aminotransferase, γ-glutamyl transpeptidase, alkaline phosphatase, amylase, blood urea nitrogen, creatinine, and C-reactive protein. ^2^Electrocardiography and thoraco-abdominal radiography will be performed for safety evaluation during the pre-treatment observation period. ^3^Adverse events monitored will include all unfavorable events, including adverse reactions not related to the EUS-FNA procedure. *EUS-FNA* endoscopic ultrasound-guided fine-needle aspiration

### Safety analysis

The severity of adverse events will be graded according to the guidelines issued by the American Society for Gastrointestinal Endoscopy [12]. The incidence rate and proportion of adverse events during follow-up will be calculated for the safety analysis set, both overall and stratified by severity. Clopper-Pearson exact 95% confidence intervals will be estimated for these occurrence proportions.

### Exploratory analysis

Exploratory subgroup analyses will be conducted to investigate the interaction between treatment effects and background factors. In principle, median values will be used for the stratification of the study sample into subgroups according to each factor of interest. Since the subgroup analyses are not statistically powered and no multiplicity adjustment is performed, the results of these analyses will only be interpreted as exploratory. In subgroup analyses, the odds ratio will be used as a summary of therapeutic effects. A Forest plot will be used to summarize the point estimate and 95% confidence interval for each subgroup. The factors and cutoff values to be used for exploratory analysis will be established in a separate statistical analysis plan.

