### Treatment allocation and blinding

Each subject will be assigned to either of the treatment methods at a ratio of 1:1 according to a web-based registration program system (based on dynamic allocation by the minimization method). Dynamic allocation by the minimization method is designed to minimize imbalance between treatments taking stratification factors into account. For assignment to prevent large bias. Based on the baseline factors for treatment allocation, including the diameter of tumor, site where the tumor is located, pattern of contrast computed tomography, and institution, an imbalance score is computed. The treatment with the lowest imbalance score is assigned.

The registration secretary will strictly control the program to prevent leaking of the assignment information. Blinding will not be used in this study.

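### For continuous factors, the default median split is a data-dependent and inefficient way to study interaction with the needle effect

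*Protocol article*

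**What the plan says.** The relevant text is in the Exploratory analysis section of the protocol article.

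- Purpose: "Exploratory subgroup analyses will be conducted to investigate the interaction between treatment effects and background factors".
- Default method: "In principle, median values will be used for the stratification of the study sample into subgroups according to each factor of interest". Each subgroup is then summarised by an odds ratio with a 95% confidence interval in a forest plot.
- Deferral: "The factors and cutoff values to be used for exploratory analysis will be established in a separate statistical analysis plan".
- Status: the section says that the analyses are unpowered and carry no multiplicity adjustment, and that "the results of these analyses will only be interpreted as exploratory".

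The section on treatment allocation and blinding lists the minimisation factors, "including the diameter of tumor, site where the tumor is located, pattern of contrast computed tomography, and institution". It does not say whether diameter was put into categories for this purpose, or at what values.

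**The concern.** The purpose is to study interaction, that is, how the needle effect changes across a background factor. For a continuous factor, the stated default replaces the measured value by above or below the median and compares two odds ratios.

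This has two costs. First, a median of the study sample is known only after enrolment and shifts with case mix, so it is not a threshold chosen in advance on clinical or design grounds. For tumour diameter it also need not coincide with whatever levels the minimisation balanced. Second, a patient just above the median counts the same as one far above it, so much of the information about a trend in effect is lost.

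At stake is whether a real gradient in needle effect, for example across lesion size, would be noticed. The analysis is short of power to begin with, so avoidable loss matters more here.

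**Working it through.** **1. The plan's own figure.** The article gives no figure for the subgroup analyses. Its only sample size is for the primary comparison: 75% against 85%, two-sided 5%, 80% power, 250 per group (Sample size calculation). With the pooled-variance formula and mean rate 0.80:

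n = [1.960·√(2·0.80·0.20) + 0.842·√(0.75·0.25 + 0.85·0.15)]² / 0.10² = (1.109 + 0.472)² / 0.01 ≈ 250 per group.

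This reproduces the stated number, and the power at 250 per group is 80.0%. The 500 patients, the 1:1 ratio and the two rates are carried into step 3.

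**2. Information kept by a median split.** For a linear effect, the relative efficiency of the split is the squared correlation r² between the factor X and the indicator D that X exceeds its median. D has SD 0.5.

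- Normal: r = 0.3989/0.5 = 0.798, r² = 2/π = 0.637. Loss 36%.
- Uniform on (0, 1): covariance 0.375 − 0.25 = 0.125, r = 0.125/(0.2887·0.5) = 0.866, r² = 0.75. Loss 25%.
- Exponential: covariance 0.5·(1 + ln 2) − 0.5 = 0.347, r = 0.347/0.5 = 0.693, r² = 0.480. Loss 52%.
- Lognormal with log-SD 0.4 and 0.5 (by simulation): r² = 0.557 and 0.517. Loss 44% and 48%.

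In terms of 500 patients, the split is worth about 500·0.637 = 318 for a normal factor, 375 for a uniform one and 240 for an exponential one. A right-skewed measurement would therefore lose more than a third.

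**3. Effect on interaction power.** Simulated model: logit(p) = ln 3 + 0.636·needle + 0.3·x + b·needle·x. Here ln 3 is the logit of 75%, and 0.636 = logit(0.85) − logit(0.75). The factor x has mean 0 and SD 1. There are 250 patients per arm, a two-sided 5% Wald test of the interaction, and 3,000 replicates.

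| Factor | Slope b per SD | Continuous term | Median split | Efficiency |
|---|---|---|---|---|
| Normal | 0.4 | 38% | 26% | 0.63 |
| Normal | 0.6 | 69% | 48% | 0.62 |
| Uniform | 0.4 | 39% | 28% | 0.73 |
| Uniform | 0.6 | 69% | 55% | 0.71 |

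The simulated efficiencies agree closely with step 2.

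**4. What the inputs mean.** The distributions, the main-effect slope of 0.3 and the interaction slopes are assumptions. A slope of 0.6 is strong: the needle odds ratio would be exp(0.636 − 0.6) = 1.04 at one SD below the mean and exp(0.636 + 0.6) = 3.44 at one SD above. At 0.4 the values are exp(0.236) = 1.27 and exp(1.036) = 2.82.

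**The case against.** The strongest answer is that the protocol hands factors and cut-offs to a separate analysis plan. That plan is not shown and may already hold better cut-offs and a formal interaction test. The words at the start of "In principle, median values will be used for the stratification of the study sample into subgroups according to each factor of interest" also mark a default that allows exceptions. The analysis is labelled exploratory, and even the continuous term is underpowered unless the interaction is very strong. Finally, the simulation builds in a linear trend, the case that favours the continuous term.

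Much of this stands, and it rules out several stronger readings.

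- A reader might infer that the median rule disregards the diameter factor used in the minimisation. The article does not support this. It gives no diameter levels to set against a median, the subgroup section does not name diameter, and the analysis plan is free to use the allocation levels. All that can be said is that the two need not match.
- A reader might infer that no interaction test will be done because only odds ratios per subgroup are described. A condensed article does not show that.
- A reader might infer that practice guidelines would rest on these subgroups. The article ties its guideline aim to needle choice overall.
- The loss does not concern tumour location, CT pattern or institution, which would not ordinarily be cut at a median.

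The objection does not remove the default itself. Leaving cut-offs to a later document does not withdraw a stated rule that points that document towards the median. The exploratory label covers multiplicity and low power; it gives no reason to give up more power.

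**Conclusion.** The point holds as a minor, inexpensive improvement to a stated default, limited to continuous factors. A median split makes the cut depend on the sample and, for a linear effect, loses about 36% of the information with a normal factor, with a range of about 25% (uniform) to 52% (exponential). At 500 patients with a normal factor, that is 69% against 48% power for a slope of 0.6 log-odds per SD, or 38% against 26% for 0.4.

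These sizes rest on assumed distributions and slopes that the article does not give, and on linearity. If the true effect were a step near the median, the split would not be at this disadvantage. The primary analysis and the sample size are unaffected, and the subgroup results stay exploratory under either method.

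**What to change.** Reword the default in the Exploratory analysis section and carry it into the separate analysis plan:

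- For continuous factors, estimate the needle-by-factor interaction in the logistic model with the factor kept continuous, and report the estimate with its 95% confidence interval.
- Keep the forest plot as a display, with cut-offs prespecified in the analysis plan. For tumour diameter, use the minimisation levels if diameter was categorised there.
- Check the linearity assumption on the log-odds scale, since the continuous term depends on it.

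The cost is a change of wording, a few extra model terms and the linearity check. No new data are needed, and the exploratory label should stay.

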### Monitoring

Visit monitoring will be performed once a year by an independent data monitoring committee. The monitoring committee will collect information on the status of accumulation, inclusion/exclusion criteria, serious adverse events, etc., and strive to provide feedback to participating institutions for early resolution if there are any problems. The monitoring committee will also report the serious adverse events to the committee of efficacy and safety assessment.

## Discussion

The choice of the most suitable needle for the diagnosis of pancreatic masses remains controversial. Several factors may affect the results of EUS-FNA biopsy, including the nature of the target lesion, the experience of the endoscopic expert, the type of needles used, the number of needle passes, and the availability of an on-site cytologist or pathologist. Moreover, specimen processing can vary between institutions, which may be a particularly relevant confounder for the diagnostic ability of EUS-FNA because the specimen collected via needle aspiration is minute. One important advantage of our study is that all samples analyzed are first-pass samples obtained using the same procedure and subjected to histologic analysis in a single facility staffed by experienced pathologists. Furthermore, the study design prevents selection bias because candidates will be recruited from among consecutive patients indicated for EUS-FNA. Finally, the study design prevents information bias because the pathologists will be blinded to the type of needle used.

Some limitations of the present study design should be mentioned. First, a final pathological diagnosis may not be available for all participants (e.g., patients who do not undergo surgery because the mass is deemed to be benign or because of other reasons such as high surgical risk or refusal of surgical treatment). Thus, a minimum of 12 months of clinical follow-up will be conducted to help establish the final diagnosis. To prevent dropout during follow-up, we will carefully monitor the recruitment process, ensure that fully informed consent is obtained, and check that complete registration information is adequately recorded. Second, the study will not consider cytology evaluation (including rapid on-site evaluation). Cytology evaluation is a very important examination that can improve the diagnostic efficacy of EUS-FNA [13]. In the present study, however, we will only evaluate the histology of the whole sample obtained in the first needle pass. The reason for this approach is that the aim of our study is to compare the diagnostic accuracy of EUS-FNA when using different needles, without the added potential benefit of cytology, which may be difficult to quantify. Third, only the results of the samples obtained in the first needle pass will be analyzed. At present, EUS-FNA best practice requires multiple passes [14] because the first pass is insufficient to diagnose pancreatic tumors in some patients. However, to establish a simple set of conditions that allow applying strictly standardized methods in clinical practice, only first-pass data will be evaluated in this study to determine whether the use of Franseen needles rather than conventional needles improves diagnostic accuracy. Results obtained from subsequent passes, in combination with imaging results and follow-up outcomes, will be used to determine the final diagnosis in patients who do not undergo surgery.

This trial will compare the diagnostic accuracy of EUS-FNA biopsy in pancreatic solid lesion samples obtained using conventional needles versus Franseen needles. The outcomes of this study may provide insight into the optimal needle choice for evaluating the malignancy of pancreatic solid lesions, thus aiding in the development of practice guidelines for pancreatic diseases.

### Trial status

Protocol version number: 01, November 26, 2017.

Patient enrollment began on July 17, 2018 and is expected to be completed by November 26, 2019.

## Data Availability

The datasets generated during the study will be available from the corresponding author on reasonable request after termination of data collection.

## Abbreviation

EUS-FNA: Endoscopic ultrasound-guided fine-needle aspiration
